***Secondary outcomes***

The secondary outcomes include QoR-40 score on POD 2 and POD 3, levels of proinflammatory cytokines (tumor necrosis factor-α, interleukin -1β, and interleukin -6), hemodynamic parameters, arterial and end tidal carbon dioxide pressure, pain scores at rest and while coughing, extubation time , length of PACU stay, ramsay sedation score on awakening, awakening time , adverse events (postoperative nausea and vomiting, headache, respiratory depression ,hypoxemia).

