***Sample size estimation***

The primary outcome that will be assessed in this study is the QoR-40 score on postoperative day (POD) 1. Previous studies reported that the minimal clinically important difference (MCID) of QoR-40 score was 6.3 points[10], based on our institutional data, the Standard Deviation was 9.3 points. Based on this assumption, 36 patients in each group would be required with a power of 80% and at an α level of 0.05. To allow for 10% possible dropouts, a total of 80 patients (n = 40 in each group) will be enrolled. The sample size is calculated using the PASS software (version 15.0.5, NCSS, LCC, Kaysville, UT).

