***Statistical analysis***

The demographic data and baseline characteristics will only be expressed using descriptive statistics and will not be compared between groups. According to the data distribution, continuous data will be expressed as means and standard deviations, or median and interquartile ranges. Categorical data will be presented as numbers and percentages. The differences between groups will be analyzed by independent t-test, repeated measures analysis of variance, or Mann Whitney rank sum test, Chi-squared test, or Fisher exact test as appropriate. All data will be analyzed using the SPSS software (version 21.0; IBM SPSS, Chicago, IL) by the independent statistician. A two-sided P value < 0.05 indicates a statistically significant difference.

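### For the serial secondary outcomes, the only joint method listed is repeated measures ANOVA, which in its standard form drops incomplete series; a mixed model would use all values (minor)

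*Protocol*

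**What the plan says.** The Statistical analysis section gives one list of tests for all outcomes: "The differences between groups will be analyzed by independent t-test, repeated measures analysis of variance, or Mann Whitney rank sum test", followed by the chi-squared and Fisher tests, to be chosen as appropriate. No test is tied to an outcome. On software it says "All data will be analyzed using the SPSS software (version 21.0; IBM SPSS, Chicago, IL) by the independent statistician", without naming a procedure. It gives no rule for incomplete series.

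Several secondary outcomes are serial. "The secondary outcomes include QoR-40 score on POD 2 and POD 3, levels of proinflammatory cytokines" opens a list that also includes haemodynamics, arterial and end-tidal CO2, and pain scores. Data collection and registration, with the Appendix A schedule, sets the times:

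- QoR-40 at 24, 48 and 72 h, with a preoperative score.
- Pain scores at 2, 6 and 24 h.
- Cytokines at 2, 6 and 24 h, with a preoperative sample in Appendix A.
- MAP, HR, BIS, ETCO2 and PaCO2 at five times: baseline, 30 and 60 minutes into surgery, end of surgery, and after extubation.

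The Sample size estimation section expects some loss: "To allow for 10% possible dropouts, a total of 80 patients (n = 40 in each group) will be enrolled".

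**The concern.** Classical repeated measures ANOVA, as in the SPSS general linear model procedure, needs a value at every time point for every patient. A patient with valid 2 h and 6 h cytokines but no 24 h sample contributes nothing. A patient who misses the 72 h QoR-40 also leaves the POD 1 and POD 2 part of that analysis. Data already collected are wasted, and the estimate is safe only if the remaining patients are representative.

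The protocol's own design makes gaps likely, apart from ordinary dropout. An operation shorter than 60 minutes cannot supply the 60-minute reading. ETCO2 is requested at baseline and after extubation, while the Anesthesia and monitoring methods section has end-tidal CO2 monitored after intubation. If those values are absent, a five-point ETCO2 analysis has few or no complete cases. The 48 h and 72 h questionnaires can be missed in the usual way.

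The cytokine comparison is part of the stated objective, and QoR-40 on POD 2 and POD 3 is the first secondary outcome listed. The choice of method therefore matters for results that will be reported.

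**Working it through.** **1. The plan's own figure.** Inputs from Sample size estimation: difference 6.3, SD 9.3, power 80%, α 0.05 (two-sided, from Statistical analysis). The normal approximation gives 35 per group. The exact noncentral t power is 79.8% at 35 and 80.9% at 36, so the stated 36 reproduces. With dropout, 36/0.9 = 40 per group, or 80 in total.

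**2. What the 10% dropout does.** If 10% of whole patients are lost, 40 × 0.9 = 36 per group remain. Power for 6.3 points at one time point is then 80.9%, against 84.9% with all 40. This loss is already allowed for.

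**3. Gaps beyond that.** The protocol gives no rate. Assume each time point is missed independently with probability p. The complete-case fraction for k time points is (1 − p)^k:

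| p (assumed) | k = 3 | k = 4 | k = 5 |
|---|---|---|---|
| 2% | 94% | 92% | 90% |
| 5% | 86% | 82% | 77% |
| 10% | 73% | 66% | 59% |

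At 5%, complete cases per arm are 40 × 0.857 = 34.3, 40 × 0.815 = 32.6 and 40 × 0.774 = 31.0. With the protocol's 6.3 and 9.3 as a yardstick at a single time point, t-test power at these sizes is about 79%, 77% and 75%. Using everyone observed at that time point keeps 40 × 0.95 = 38 per arm and 83.0%. The cost is about 4 to 8 percentage points. The protocol plans no power for the serial outcomes, so this only shows scale.

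**4. Bias.** Loss completely at random gives none: in simulation the complete-case estimate stayed at 6.3. For loss that depends on recovery, the assumptions were a true difference of 6.3 on each of POD 1 to 3, SD 9.3, correlation 0.6, and the 72 h score missing more often after a good 48 h score (logistic). The slope is the log-odds of missing per SD of the 48 h score. The estimand is the group effect averaged over the three days.

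| Slope | 10% missing at 72 h | 23% missing at 72 h |
|---|---|---|
| 0.5 | 6.2 | 6.1 |
| 1.0 | 6.0 | 5.7 |
| 1.5 | 5.8 | 5.4 |

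The likelihood-based estimate was 6.3 in every cell. A slope of 1.5 is steep: the odds of missing 72 h rise e^1.5 ≈ 4.5-fold per SD. The 23% rate has no basis in the document and only shows the trend. The standard error of this group effect with 40 per arm is 9.3 × √((1 + 2 × 0.6)/3) × √(2/40) ≈ 1.8. The largest bias at 10% missing, 6.3 − 5.8 = 0.5, is therefore under a third of a standard error.

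**The case against.** The strongest reply is that the protocol does not commit itself to deleting anyone. The tests are listed for use as appropriate, no SPSS procedure is named, and a t-test or Mann-Whitney test at each time point would use every patient observed then. QoR-40 on POD 2 and on POD 3 are listed by day, which fits that reading. Handling of incomplete series may also sit in a statistical analysis plan that is not at hand.

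Much of this stands. A reader might infer that the protocol prescribes discarding incomplete patients; it does not, and deletion is a property of the standard procedure. A reader might also infer that the expected 10% dropout takes the trial below its planned power. It does not, because 40 are enrolled to keep 36. Nor is the primary comparison at risk, since it needs no repeated measures test. It would also be too strong to say that the serial group effects are biased: that needs loss related to recovery, and the document gives no evidence on that. Most series end in theatre or at 24 h, so loss related to recovery chiefly concerns the 48 h and 72 h QoR-40.

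The choice of method still stands as a point. Where several time points are analysed jointly, repeated measures ANOVA is the method named, and a later plan would have to replace or supplement it to keep incomplete series. The 60-minute reading and the ETCO2 times create gaps that do not depend on anyone dropping out.

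**Conclusion.** The point holds at minor severity and for the serial secondary outcomes only. The named joint method wastes data when series are incomplete, and the design makes incomplete series foreseeable. The size is modest: at an assumed 5% of values missed per time point, 14%, 18% or 23% of patients drop out of a 3-, 4- or 5-point analysis. Bias is conditional: with 10% missing at 72 h, a true 6.3 averages between about 6.2 and 5.8 as the dependence on recovery goes from weak to steep, and stays at 6.3 if loss is random. The miss rate, the within-patient correlation and the loss mechanism are assumptions. The mixed model's freedom from bias in these simulations reflects that loss depended only on the observed 48 h score; it would not be guaranteed if loss depended on the unseen 72 h score.

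**What to change.** In Statistical analysis, replace repeated measures ANOVA with a linear mixed model for repeated measures. Include group, time and group-by-time, with an unstructured within-patient covariance and a pre-stated simpler fallback (for example compound symmetry) if it does not converge. Use all observed values of randomised patients, and report the between-group difference at each scheduled time. The MIXED procedure in the stated SPSS version can fit this.

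Also reconcile the ETCO2 time points in Data collection and registration with the monitoring description in Anesthesia and monitoring methods. No model can estimate a difference at a time when nobody has a value.

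The cost is a sentence or two, with no added patients, data or software. The small downside is having to specify the covariance structure and its fallback in advance.

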**Ethical considerations and declarations**

Our research is conducted according to the principles of the Declaration of Helsinki. Written informed consent will be obtained from all participants and/or their legal representatives. The investigator must report all Serious Adverse Events (SAEs) to the sponsor (the corresponding author in the trial) immediately and inform the Ethics Committee accordingly. The organizer is responsible for the continuous safety assessment of anesthesia protocol, if SAE occurs, the test will be terminated, and if SAE occurs, the participants will be compensated.

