***Anesthesia maintenance***

Anesthesia maintenance is defined as the time from the end of induction to the cessation of anesthesia (the infusion or inhalation of anesthetic drugs will be stopped immediately after the end of surgery). Group T will receive continuous propofol infusion at a rate of 4–12 mg/kg/h for maintenance, whereas Group C will receive inhalation of sevoflurane at 1.0-3.0% for maintenance. Remifentanil will be administered at a rate of 0.05–0.2 μg/kg/min, cisatracurium and sufentanil will be added in both groups according to requirements of the surgery. The depth of anesthesia will be titrated to BIS values of 40–55 via the manual adjustment of propofol infusion or inhalation of sevoflurane. Upon completion of the surgery, all anesthetic agents will be discontinued. All patients will be provided with patient-controlled intravenous analgesia (PCIA) (1.5 μg/kg of sufentanil + 0.9% normal saline, total volume 100 ml 2 ml/h for 48 h). The self-controlled capacity and the locking time will be 0.5ml and 15 minutes, respectively.

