***Outcomes***

***Primary outcomes***

The primary outcome of this study is global Quality of Recovery-40 (QoR-40) score on POD 1. The QoR-40 contains 40 items assessing five dimensions of recovery: emotions, physical comfort, psychological support, physical independence, and pain, which scores range from 40 to 200. QoR-40 has been widely used in clinical practice and research for various surgical types and anesthesia techniques.

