***Data collection and registration***

Trained independent investigators who are unaware of group assignment will collect patients’ demographic data and baseline characteristics. The primary and secondary outcome measures as well as other non-outcome perioperative data will be collected. The values of MAP、HR、BIS、ETCO2 and PaCO2 will be recorded at five timepoints: baseline, 30 mins into the surgery, 60 mins into the surgery, the end of surgery, and immediately after tracheal extubation. Postoperative pain will be evaluated using the Numerical Rating Scale, ranging from 0 to 10 (0=no pain, 10=the most severe imaginable pain). Levels of proinflammatory cytokines and NRS will be recorded at postoperative 2,6,24h. All data will be entered into the electronic case report forms(eCRFs) under the supervision of trained research personnel. Investigators will conduct an interim analysis to make an informed decision on whether to continue the trial or modify the study design to optimize the trial results. After the completion of data registration, the electronic database will be locked. After de-identification, the database will be sent to an independent statistician for statistical analysis.

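### The protocol ends the test whenever an SAE occurs, without a relatedness condition or decision step, and without saying whether the patient's study treatment or the whole trial stops

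*Protocol*

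**What the plan says.** The rule stands in the Protocol, Ethical considerations and declarations: "if SAE occurs, the test will be terminated, and if SAE occurs, the participants will be compensated". The same section sets two duties. One is reporting: "The investigator must report all Serious Adverse Events (SAEs) to the sponsor", immediately, with the Ethics Committee informed. The other is oversight: "The organizer is responsible for the continuous safety assessment of anesthesia protocol". Neither is made a condition of termination.

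Three other sections bear on what the rule covers:

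- **Withdrawal criteria** lists three grounds: withdrawn consent or a request to leave, a limit on knowledge of group assignment, and a combined PaCO2 and pH limit during surgery. SAE is not among them.
- **Data collection and registration** has the investigators run an interim analysis to "make an informed decision on whether to continue the trial or modify the study design". It gives no safety criterion and does not mention SAEs.
- **Informed consent** provides for a revised consent form, and fresh consent to carry on, if new safety evidence significantly changes the benefit-risk assessment.

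**The concern.** The clause makes termination the automatic result of any SAE, whatever its cause or arm, and leaves the object of termination undefined. The two possible meanings call for different actions.

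- **Whole trial.** A single surgical complication with no link to propofol or sevoflurane would stop enrolment, and the comparison would have less power than planned.
- **Individual patient.** The clause does not say what stops. After surgery several study elements are still running: sufentanil PCIA for 48 h, cytokine sampling up to 24 h, and the questionnaire. "The primary outcome of this study is global Quality of Recovery-40 (QoR-40) score on POD 1", and "The secondary outcomes include QoR-40 score on POD 2 and POD 3". If staff took termination to include follow-up, QoR-40 scores would be lost in patients who are likely to recover poorly, so the missing data would be related to the outcome.

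How to report an SAE is clear. What is unclear is what termination means once the report is made. That is better settled before an event than after one.

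**Working it through.** **Inputs.** From Sample size estimation: difference 6.3 points, SD 9.3, alpha 0.05, power 80%, 36 per group, 10% dropout, 80 enrolled. From Statistical analysis: two-sided testing. The protocol gives no SAE rate, so every per-patient risk *p* below is an assumption. The eligibility limits (age 18–65, elective surgery, severe organ disease excluded) favour the lower values.

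**Step 1: the plan's own figure.** The two-sample t-test solution for 6.3/9.3 at 80% power is 35.19, so 36 per group. Then 36/0.9 = 40 per group, 80 in total. The stated size reproduces. Power at 36 evaluable per group is 0.809.

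**Step 2: trial reading, chance of completing.** With independent risk *p*, P(no SAE in 80) = (1 − p)^80. Early stopping becomes more likely than not when this falls below 0.5, that is above p = 1 − 0.5^(1/80) = 0.0086, or 0.86%.

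**Step 3: trial reading, average power.** Suppose the trial stops at the first SAE, patient *k*, and whatever has accrued is analysed with an equal split and 10% dropout:

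average power = Σ(k = 1 to 80) p(1 − p)^(k−1) × power(k enrolled) + (1 − p)^80 × power(80 enrolled).

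| Assumed risk per patient | P(complete 80) | Average power |
|---|---|---|
| 0.1% | 92% | about 78% |
| 0.5% | 67% | about 69% |
| 1% | 45% | about 60% |
| 2% | 20% | about 45% |
| 5% | 2% | about 25% |

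Average power moves by about one or two points depending on whether group sizes are rounded to whole patients and how very small samples are handled; at 1% it is 59 to 60%. It falls below 75% above a risk of about 0.23%, and below 70% above about 0.45%.

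**Step 4: patient reading, number lost.** Expected patients with an SAE = 80p: 0.08, 0.4, 0.8, 1.6 and 4.0 over the same range. The dropout allowance is 80 − 72 = 8. If four were lost beyond that allowance, power would still be about 0.785 (32 against 36, or 34 against 34).

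**Step 5: patient reading, bias.** Omitting one patient whose score is *D* below the rest shifts a 36-patient arm mean by D/36. At 1 SD this is 9.3/36 = 0.26 points, and at 2 SD it is 18.6/36 = 0.52 points. The extreme case of four patients at 2 SD, all in one arm, gives 4 × 18.6/36 = 2.07 points. The planned difference is 6.3.

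**The case against.** A reader might infer that the protocol orders the whole trial to stop at its first SAE. The text does not support that as the intended meaning. A duty to report all SAEs, in the plural, and a continuous safety assessment fit poorly with a trial that could have only one SAE. The clause directly before the rule concerns the anaesthesia protocol, and the clause after it compensates participants. The decision to continue is placed in an interim analysis. The consent section answers even a significant change in benefit-risk with revised consent and continuation.

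This argument largely stands, with two limits. Withdrawal criteria, where a patient-level rule would be expected, does not list SAE. The consent section speaks of new safety evidence, not of an SAE in this trial. So the balance leans to the patient reading without settling it.

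The size of the trial-level loss is also open to challenge, and fairly. The rates are assumed. The large losses need both the less supported reading and the higher rates: at 0.1% the trial completes 92% of the time and loses about 3 points of power. The average-power figures further assume a mechanical stop and an analysis of whatever has accrued, neither of which the protocol specifies.

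A second tempting inference is that QoR-40 data will be lost after an SAE. The text does not say that follow-up stops, so this loss is possible but not prescribed.

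**Conclusion.** The defect is real but minor. The protocol states a termination rule that has no relatedness condition, no decision step and no defined scope, and no other section supplies them.

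On the better-supported patient reading, the consequence is at most a small outcome-related loss: 0.08 to 4 patients over the assumed risks of 0.1 to 5%, inside the 8-patient allowance, with 0.26 to 0.52 points of bias per lost patient scoring 1 to 2 SD low. On the literal trial reading, which is less well supported but not excluded, assumed risks of 0.1 to 1% would cut the chance of completing enrolment to between 92 and 45%, and average power to between about 78 and 60%. The reason to act is that one sentence removes both problems at almost no cost.

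**What to change.** Replace the termination clause with:

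> If an SAE occurs, study treatment is stopped or changed for that patient where clinically needed; the patient stays in follow-up, including QoR-40 on POD 1–3, unless consent is withdrawn. A single SAE does not by itself end the trial; suspension or termination is decided after review of the SAE, including its relatedness to the study anaesthetic, by the sponsor and the Ethics Committee.

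Keep the compensation clause as it is. The essential changes are to separate the patient from the trial and to keep follow-up going. The review step uses the two bodies that already receive SAE reports or notice under the protocol.

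Cost: amendment wording and an Ethics Committee notification. No extra patients, visits or measurements are needed.

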**Informed consent**

Researchers will obtain signed informed consent from each subject before surgery, and be responsible for explaining the purpose, methods, expected benefits and potential risks of the clinical trial to the subjects. If the new safety study indicates that the benefit risk assessment has changed significantly, the informed consent form will be reviewed and modified, and all study participants will be provided with access to new information. Participants will receive the revised informed consent form, and researchers will obtain their informed consent form to continue the study. The study participants will be screened according to the inclusion and exclusion criteria after signing the informed consent.

**Appendix A**

| Table 1 Schedule of patient enrolment, study interventions and outcome assessment | | | | | | | | | |
| --- | --- | --- | --- | --- | --- | --- | --- | --- | --- |
|  | Study period |  |  |  |  |  |  |  |  |
|  | Enrolment | Allocation | Post-allocation |  |  |  |  |  |  |
|  |  | 2 hours |  |  |  |  |  |  |  |
|  | Preoperative | before |  |  | POS | POS | POS | POS | POS |
| Time point | visit | surgery | intraoperatively | PACU | 2h | 6h | 24h | 48h | 72h |
| Patient enrolment |  |  |  |  |  |  |  |  |  |
| Eligibility criteria | **×** |  |  |  |  |  |  |  |  |
| Written informed  consent | **×** |  |  |  |  |  |  |  |  |
| Demographic data | **×** |  |  |  |  |  |  |  |  |
| Baseline  characteristics | **×** |  |  |  |  |  |  |  |  |
| Randomisation/ |  | **×** |  |  |  |  |  |  |  |
| allocation |  |  |  |  |  |  |  |  |  |
| Study interventions |  |  |  |  |  |  |  |  |  |
| Total intravenous |  |  | **×** |  |  |  |  |  |  |
| anaesthesia |  |  |  |  |  |  |  |  |  |
| Inhalation |  |  | **×** |  |  |  |  |  |  |
| anesthesia |  |  |  |  |  |  |  |  |  |
| Outcome assessment |  |  |  |  |  |  |  |  |  |
| QoR-40 scores | **×** |  |  |  |  |  | **×** | **×** | **×** |
| Postoperative pain  scores |  |  |  |  | **×** | **×** | **×** |  |  |
| Length of PACU  stay |  |  |  | **×** |  |  |  |  |  |
| Levels of | **×** |  |  |  | **×** | **×** | **×** |  |  |
| proinflammatory |  |  |  |  |  |  |  |  |  |
| cytokines |  |  |  |  |  |  |  |  |  |
| Hemodynamic |  |  | **×** |  |  |  |  |  |  |
| parameters |  |  |  |  |  |  |  |  |  |
| ETCO2 |  |  | **×** |  |  |  |  |  |  |
| PaCO2 |  |  | **×** |  |  |  |  |  |  |
| Awakening time |  |  | **×** |  |  |  |  |  |  |
| Extubation time |  |  | **×** |  |  |  |  |  |  |
| Level of sedation |  |  | **×** |  |  |  |  |  |  |
| PONV |  |  |  |  |  |  | **×** |  |  |
| Headache |  |  |  |  |  |  | **×** |  |  |
| Hypoxemia |  |  |  |  |  |  | **×** |  |  |
| Respiratory depression |  |  |  |  |  |  | **×** |  |  |
| According to SPIRIT statement of defining standard protocol items for clinical trials. | | | | | | | | | |
| QoR-40, 40 items of Quality of Recovery;PACU, post-anaesthesia care unit;  PONV, postoperative nausea and vomiting; POS, postoperative; | | | | | | | | | |
| ETCO2,end-tidal carbon dioxide;PaCO2,partial pressure of arterial carbon dioxide. | | | | | | |  |  |  |
| SPIRIT, Standard Protocol Items: Recommendations for Interventional Trials. | | | | | | | | | |

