***Recovery of anesthesia***

After tracheal extubation, patients will be transferred to a post-anesthesia care unit (PACU) and receive oxygen supplementation of 3 L/min via a nasal catheter. When the Steward awakening score ≥4 points is reached, patients will be discharged from the PACU to the surgical wards.

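### PONV, headache, hypoxemia and respiratory depression are scheduled only at 24 h with no stated window, so non-serious events after 24 h go uncollected and early transient ones may be missed

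*Protocol*

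**What the plan says.** Secondary outcomes lists "adverse events (postoperative nausea and vomiting, headache, respiratory depression ,hypoxemia" among the secondary outcomes. It gives no time window, recall period or definition for any of the four. Data collection and registration sets times for haemodynamics, carbon dioxide, cytokines and pain, but not for these events.

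The only timing is in Appendix A, Table 1. The rows for PONV, headache, hypoxemia and "Respiratory depression" each have one mark, under 24 h. The cells for PACU, 2 h, 6 h, 48 h and 72 h are empty.

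The same table uses those contacts for other outcomes:
- PACU: "Length of PACU stay".
- 2 h and 6 h: "Levels of proinflammatory cytokines and NRS will be recorded at postoperative 2,6,24h".
- 48 h and 72 h: QoR-40.

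Anesthesia maintenance gives every patient sufentanil PCIA, "total volume 100 ml 2 ml/h for 48 h". It adds: "The self-controlled capacity and the locking time will be 0.5ml and 15 minutes, respectively". Both randomised maintenance agents stop at the end of surgery. Recovery of anesthesia says that after extubation "patients will be transferred to a post-anesthesia care unit (PACU) and receive oxygen supplementation of 3 L/min". Ethical considerations and declarations requires immediate reporting of serious adverse events and sets out no route for non-serious ones.

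**The concern.** Hypoxemia and respiratory depression come and go, and are seen when they happen or not at all. A patient asked at 24 h cannot reliably report a desaturation in the PACU, and no chart review is specified. Later, the opioid infusion continues beyond the last scheduled look at opioid-related events.

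Two things are at stake. The first is the absolute incidence of these events, which the trial would report as secondary outcomes. The second is the comparison between anaesthetics, which depends on the hours soon after emergence, when the effect of the maintenance agent is expected. A statistical analysis plan can choose which window to analyse, but it cannot recover events that were never recorded.

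**Working it through.** **1. Position of the marks.** Table 1 has nine time-point columns: preoperative visit, 2 h before surgery, intraoperative, PACU, 2 h, 6 h, 24 h, 48 h and 72 h. In all four rows the only mark is in the seventh, 24 h. That is one of six postoperative contacts.

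**2. Duration of PCIA.** I take the pump as started at the end of surgery, and the postoperative hours as counted from there.
- Plan's figure: 2 ml/h × 48 h = 96 ml of the 100 ml reservoir, so the 48 h is consistent with the volume.
- Background infusion alone: 100 / 2 = 50 h.
- Maximum demand: 60 / 15 = 4 demands per hour; 4 × 0.5 ml = 2 ml/h extra; 100 / (2 + 2) = 25 h.
- Demands available before the reservoir falls short of 48 h: (100 − 96) / 0.5 = 8.

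Every permitted pattern of use therefore outlasts the 24 h check. The time after it is (48 − 24) / 48 = 50% of the nominal period, falling to (25 − 24) / 25 = 4% at maximum demand. These are shares of hours, not of events; the protocol gives no event rates or timing.

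**3. Capture under the two readings of the mark** (assumed inputs, for illustration).
- Any occurrence from 0 to 24 h: if 5% to 30% of events start after 24 h, then 95% to 70% are captured, provided early events are fully recalled or charted.
- State at 24 h only: with onset uniform over 48 h and an event lasting d hours, the share captured is d / 48. For d = 0.5 this is 1%; for d = 4 it is 8%. An event that starts by 6 h and lasts at most 4 h is over by 10 h and is never seen.

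**4. Effect on the comparison between arms.**
- Early events under-recorded equally in both arms, with a share c captured: the observed difference is c × (p1 − p2). With assumed true risks of 40% and 20% and c = 0.70, the observed risks are 28% and 14%, and the difference falls from 20 to 14 points.
- Late events, with the same risk q in both arms: 0 to 48 h incidence is p + (1 − p)q, so the difference is (p1 − p2)(1 − q). With q = 10%, 0.40 + 0.60 × 0.10 = 46% and 0.20 + 0.80 × 0.10 = 28%, a difference of 18 points. Leaving late events out does not shrink the contrast; pooling them in does.

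**The case against.** The strongest reply is that one mark need not mean one observation. Haemodynamic and carbon dioxide values are taken at five times yet have a single mark under the intraoperative column, so a mark at 24 h could stand for occurrence during the first 24 h. This stands in part: the protocol does not exclude that reading, and under it PACU, 2 h and 6 h events fall inside the window. The analogy is weak, however. The intraoperative column is a period, whereas the postoperative columns are time points, and the pain and cytokine marks at 2, 6 and 24 h denote separate assessments.

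Second, PCIA is the same in both arms and the randomised agents stop at the end of surgery. This stands. A reader might infer that the gap from 24 to 48 h pulls the difference between arms towards none. The protocol does not support that, and on the premise that late events are common to both arms a 24 h window is reasonable for the comparison.

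Third, a reader might infer false reassurance on safety. That goes too far: serious events must be reported immediately, and PaCO2 after extubation and the sedation score on awakening give some objective information on emergence. Neither is a record of the four events.

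Fourth, exact windows are often left to the analysis plan. That holds for the analysis, but not for the collection schedule, which the protocol fixes.

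**Conclusion.** The point holds as a cheap improvement. Whichever way the mark is read, non-serious PONV, headache, hypoxemia and respiratory depression after 24 h have no scheduled collection, although PCIA nominally runs for another 24 of its 48 h. Loss of early events is possible but not established: it follows if the mark is a check at one moment, and otherwise depends on recall or charts that the protocol does not mention.

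The main consequence is that absolute incidence is under-described. Attenuation of the contrast between arms is a risk for early events only. A flat statement that events are missed would go beyond the text, because the extent depends on an undefined window: the illustrative capture runs from about 1% to 95% across the two readings, all on assumed durations and timing. The primary outcome and the sample size are unaffected.

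**What to change.** In Table 1, mark the four events at PACU, 2 h, 6 h, 24 h and 48 h, and state that each entry covers any occurrence since the previous contact (for PACU, since extubation). Report 0 to 24 h incidence by arm as the main comparison, since that is where the anaesthetic contrast is expected, and 0 to 48 h incidence by arm as a safety description. State the same windows in Secondary outcomes so that text and table agree.

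The cost is a few extra eCRF fields and slightly more assessor time. All five contacts are already scheduled for other outcomes, so no visit is added and treatment does not change. The protocol does not say whether the 48 h QoR-40 contact is at the bedside; if it is not, the entry for respiratory events should come from the ward record.
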